### Additional analyses

Exploratory correlational analyses will also be conducted to examine relationships between changes from preintervention to postintervention on the various measures (eg, the relationship between change from pre–post HRV RMSSD and pre–post DASS scores).

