**Trial registration number:**

NCT05674071.

STRENGTHS AND LIMITATIONS OF THIS STUDYThis study will investigate the utility of osteopathic techniques for improving mental health, in the absence of any existing pain.The techniques being compared are based on previous literature and evidence.Due to this being a feasibility study, only a small number of participants are being recruited which will lead to low statistical power of the results.As the study is focused on comparing four interventions in a feasibility setting, there will be no control group comparison.

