### Objectives

This study aims to investigate the feasibility and acceptability of four osteopathic interventions for adults with mild to moderate mental health symptomatology. A secondary aim is to evaluate the influence of these four interventions on physiological factors including HRV and interoception. The study will aim to evaluate their effectiveness in improving psychological outcomes including depression, stress, anxiety, negative affect (NA) and psychological flexibility. It is first hypothesised that the interventions will be feasible and acceptable to participants. It is also hypothesised that the interventions will induce psychophysiological relaxation by significantly increasing HRV and improving IAc. No specific predictions are made about blood pressure (BP) as data on this is only being collected to check that we are within safe BP bounds, that is, for participant safety. A final hypothesis is that the four interventions will lead to similar improvements in depression, anxiety, stress and NA.

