### Trial design

This is a feasibility study, which will use an explanatory sequential mixed-methods approach. In this approach, the quantitative aspect forms the first part of the study, followed by a qualitative aspect to help provide further explanation and depth.^32^ For the quantitative aspect, the study will use a parallel, randomised design with an equal proportion of participants allocated to each of the four conditions. The qualitative aspect will be completed by interviewing the participants of the intervention and the practitioner delivering them.

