### Sample size

The study will aim to recruit 32 participants. This number of participants is generally deemed sufficient for feasibility studies^48^ and would represent approximately 10% of the sample size required in a full trial.^49^ This sample size also falls within what is practical given the available resources.

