## Statistical methods

### Outcomes

Statistical analysis will be conducted using IBM SPSS (V.27). Means and SD will be reported for demographic data that includes gender, age and ethnicity. For the main analysis, data will first be examined for normality using the Shapiro-Wilk test. If data are skewed, logarithmic transformation will be used, otherwise, analysis will continue without any transformation. HRV data will be preprocessed, and inspected for any potential artefacts, and these will be removed if identified. RMSSD will be calculated on the preprocessed artefact removed data using Kubios V.3.5 (https://www.kubios.com/) via Matlab V.R2021a. IAc will then be calculated using the formula: IAc=1/4 Σ [1−(|recorded heartbeats−counted heartbeats|/recorded heartbeats)]. The psychometrics will be totalled according to the relevant questionnaire instructions and subscales.

The main analysis will comprise of seven separate mixed design two (preintervention and postintervention) by four (AVHT, STM, CST, combination (please see: Interventions section for full details of these interventions.)) analysis of covariance (ANCOVA) models. This will comprise of five separate ANCOVAs for the five psychometrics (DASS, PANAS-SF, AAQ, SACS, MAIA) and another two ANCOVAs for the physiological measures of IAc and HRV (as measured by RMSSD and LF/HF ratio). Covariates will consist of (1) whether participants are currently receiving psychotherapy (yes or no) and (2) whether participants are receiving pharmacological treatment (yes or no). Significant models will be examined further using post hoc Bonferroni tests.

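### The exploratory change-score correlations do not say whether randomised arm is accounted for; pooled over arms, they could mix between-arm differences with the association within arm

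*Protocol article*

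**What the plan says.** The Additional analyses section of the protocol article is a single sentence: "Exploratory correlational analyses will also be conducted to examine relationships between changes from preintervention to postintervention on the various measures". The example it gives is "the relationship between change from pre–post HRV RMSSD and pre–post DASS scores". It does not say whether participants from the four arms are pooled, analysed arm by arm, or adjusted for arm.

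Arm does appear in the section just before, where the main models are set out: "The main analysis will comprise of seven separate mixed design two (preintervention and postintervention) by four", followed by the names of the four interventions. The covariates, psychotherapy and drug treatment, are also given for those models only. Neither the arm factor nor the covariates are carried into the sentence on correlations.

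Three other statements bear on the point:
- Sample size: "The study will aim to recruit 32 participants".
- Trial design: "an equal proportion of participants allocated to each of the four conditions".
- Objectives, on the psychological outcomes: "A final hypothesis is that the four interventions will lead to similar improvements in depression, anxiety, stress and NA".

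**The concern.** These correlations are the only stated quantitative analysis that relates change in a physiological measure to change in a psychological one, and the Introduction presents that link as the rationale of the study. With arm named for the ANCOVAs and absent here, the natural reading is a simple two-variable correlation over all participants.

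On that reading, randomised arm is a possible common cause of both changes. Suppose one technique raised RMSSD through an autonomic effect and lowered DASS for another reason, such as expectation; participants know what they received. The pooled coefficient would then differ from zero even if, among people given the same technique, those with more RMSSD change had no more DASS change than the others. A reader could take an arm difference for a link between physiology and mood.

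The Choice of comparators section gives some reason to think arms could differ. It rests the techniques on different evidence: heart rate variability for the craniosacral techniques, interoceptive accuracy for high-velocity thrust, and both psychological and heart rate variability findings for massage.

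**Working it through.** **Inputs from the article.** N = 32 (Sample size; the abstract says 30) and equal allocation to four arms, so 32 / 4 = 8 per arm. The sample size rests on convention and practicality. It has no power calculation to reproduce, and no figure is stated for the correlations.

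**Assumptions, because the article gives no values.** Two-sided alpha of 0.05; a true within-arm correlation of 0; a shift of d within-arm standard deviations of change, in the responding arm or arms, on both measures. If one measure rises and the other falls, r changes sign but not size.

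**Expected pooled correlation.** With unit variance within arm and no association within arm, r = B / (1 + B), where B is the variance of the arm means.
- One arm of four shifted: B = (1/4)(3/4)d² = (3/16)d².
- Two arms of four shifted (for instance one technique and the combination): B = (1/2)(1/2)d² = d²/4.
- All four arms shifted equally: B = 0, so r = 0.

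Two worked cases with one arm shifted:
- d = 0.5: B = 0.1875 × 0.25 = 0.047, and r = 0.047 / 1.047 = 0.045.
- d = 1: B = 0.1875, and r = 0.1875 / 1.1875 = 0.158.

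**False-positive rates.** These come from 40,000 simulated trials per scenario with 4 × 8 participants. The pooled Pearson correlation was tested on 30 degrees of freedom and the arm-centred (partial) correlation on 32 − 4 − 1 = 27.

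| Arms that respond | d | Expected pooled r | Pooled, p < 0.05 | Arm-adjusted, p < 0.05 |
|---|---|---|---|---|
| One | 0.2 | 0.007 | 5.0% | 4.9% |
| One | 0.5 | 0.045 | 5.8% | 5.1% |
| One | 0.8 | 0.107 | 9.0% | 4.9% |
| One | 1.0 | 0.158 | 14.0% | 5.0% |
| One | 1.5 | 0.297 | 39.9% | 5.1% |
| One | 2.0 | 0.429 | 75.7% | 5.1% |
| Two | 0.5 | 0.059 | 6.1% | 5.0% |
| Two | 0.8 | 0.138 | 11.8% | 5.1% |
| Two | 1.0 | 0.200 | 19.7% | 4.9% |
| All four, equally | 0.5 to 1.5 | 0 | 5.0% to 5.1% | 4.9% to 5.2% |

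The mean arm-adjusted correlation was about 0.00 in every scenario.

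**Price of adjusting.** The critical value is |r| = t / √(df + t²).
- Pooled, 30 df: t = 2.042, so 2.042 / √(30 + 4.17) = 0.349.
- Adjusted, 27 df: t = 2.052, so 2.052 / √(27 + 4.21) = 0.367.

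**The case against.** The strongest reply is that the sentence is silent and fixes nothing. A reader might infer that the plan has decided to ignore arm, but the text does not say so. A journal article may leave the adjustment set of an exploratory correlation to a fuller analysis plan. That stands, and it limits the point to a request for clarification.

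A second reply is that inflation needs the arms to differ on both measures, while the protocol hypothesises similar improvement on depression, anxiety and stress, which are the DASS outcomes in its own example. This also stands. If the hypothesis holds for one of the two measures, pooling creates no spurious correlation. But it is a hypothesis that the main models examine, it covers only the psychological outcomes, and adjustment is valid whether or not it is true.

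Third, the larger rates need differences of about 1 SD between active treatments after one session of about 30 minutes, and nothing in the article supports or excludes that. Even at 1 SD in one arm, 86% of trials would show no significant correlation.

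Fourth, pooled and adjusted correlations answer different questions. If a technique lowered DASS by raising RMSSD, adjustment would remove the between-arm part of a real link. This is fair but not decisive: a real link would also show among participants within the same arm, and the arm differences are examined in the main models. Adjustment would not remove expectation that varies between people within an arm, and "there will be no control group comparison" to help with that.

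Finally, the analysis is already labelled exploratory and the article admits low power. That is correct and is why the point is small.

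**Conclusion.** The point holds as a conditional and minor one. The article does not say how arm is handled in the change-score correlations. If they are pooled, and the arms differ in mean change on both measures, the coefficient mixes between-arm differences with the association between persons within arm.

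Inflation is absent when all arms respond alike and negligible at 0.5 SD in one arm. It becomes material at roughly 0.8 to 1 SD or more. The arm shifts, the 5% level and the zero within-arm correlation are all assumptions.

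Two stronger readings are not supported. A reader might conclude that outcomes responding to one technique are bound to correlate; they only can, and only when arms differ enough on both measures. A reader might also describe the uncontaminated quantity as an association within persons. Each participant gives one change per measure, so what can be estimated is the association between persons within arm.

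Only an exploratory analysis is affected. The primary feasibility and acceptability outcomes do not depend on it, and the main ANCOVAs already contain arm.

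**What to change.** In Additional analyses, state that the associations between changes will be estimated as partial correlations adjusting for randomised arm, or as correlations of residuals from the arm models, reported with 95% confidence intervals and kept as exploratory.

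The cost is one phrase and three residual degrees of freedom, with the small rise in the critical |r| shown above. No new data are needed. Adjustment works on masked group codes, as the main models must, so it fits the plan to reveal the allocation only after the analysis is complete.

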### Analysis of population and missing data

The study will operate on an intention-to-treat basis. All participants randomised and with preintervention data will be included in the final analysis. Any participants with missing data will be included in the analysis using the multiple imputation feature of SPSS.

## Methods: monitoring

### Data monitoring

As this study is taking place over a short duration as a feasibility study and not a full RCT, no formal committee for data monitoring is required.

### Harms

The osteopathic practitioner will inform the participants about the general potential common adverse effects of osteopathy namely some stiffness and soreness in the days following the intervention, and rare adverse events including tissue damage,^51^ in line with informed consent processes. The osteopathic practitioner will record any adverse effects on the day the intervention is received (that occur during or immediately after the intervention) in the AERF (see online supplemental material 2). Participants will also be advised to contact the PI [name] by telephone if they have any concerns or adverse events following the intervention in subsequent days after the intervention was received. If such events are reported, these will again be reported by [name] in the AERF. Any adverse events or harms that are ranked highly on severity will be reported to the ethical committee. This includes any adverse events that, for example, require hospitalisation.

### Auditing

As the study is taking place over a short duration and only at one site, no formal auditing processes are deemed necessary, though PI will have regular team meetings to ensure the study is following the research protocol at all times.

## Methods: patient and public involvement statement

Key stakeholders were consulted and involved at a very early stage of the research process. The Patient Experience and Evaluation in Research (https://www.swansea.ac.uk/humanandhealthsciences/research-at-the-college-of-human-and-health/patientexperienceandevaluationinresearchpeergroup/) group in the College of Human and Health Sciences at Swansea University were consulted. This group represented members of the public, students, and staff members, several of whom reported that they had experienced depression, anxiety or stress at some point in their lives and emphasised the need for innovative approaches to the delivery of mental health support. The feasibility design was explained to them, and they gave positive feedback about the nature of the preliminary research plan.

## Ethics and dissemination

### Research ethics approval

The protocol for this feasibility study has received ethical approval from the Department of Psychology Ethics Committee at Swansea University, ethical review reference number: 2022-5603-4810.

### Protocol amendments

Any deviations from the protocol that could impact the conduct or bias of the study will be clearly outlined and justified in the final written report. Version control of the protocol using identifiers and dates, along with a list of amendments will be clearly listed. This will enable tracking of the history of amendments and identification of the most recent protocol version.

### Consent

Participants will scan a QR code on recruitment posters or click a link via email/social media adverts that will take them to the study’s information sheet. The information sheet emphasises that participation is voluntary and that they can withdraw from the study at any stage, without needing to provide a reason. If they have any questions or concerns at this stage, they are encouraged on the information sheet to contact the research team. If they are willing to proceed, they will complete an online consent form (see online supplemental material 3).

10.1136/bmjopen-2023-071680.supp3Supplementary data

### Ancillary research

The data collected in this study will not be used for any other ancillary research.

### Confidentiality

Participants will be assigned a coded ID number to maintain confidentiality. Any records of personal identifiers such as informed consent forms will be stored separately from data with ID numbers. To limit data access to the minimum number of individuals, only the researcher [name] will have access to the data for analysis.

### Access to data

Only the researcher [name] will have access to the dataset during the study period. On completion, the collected data will be deidentified and made available on the OSF. Similarly, the SPSS statistical syntax code used will be made available on OSF.

### Ancillary and post-trial care

Participants will be fully debriefed once they have completed the study. The contact details of the research team will be provided should participants have any concerns. As the participants will be presenting with mild to moderate mental health symptoms, the debrief form will encourage participants to seek support services such as mental health charities or their general practitioner if their psychological condition deteriorates at any time.

## Dissemination policy

### Trial results

Following the completion of the study, it is anticipated to take around 2–3 months to compile the final results ready for publication in an appropriate peer-reviewed journal. The study’s results may also be used as part of presentations at any relevant conferences.

### Authorship

The authors of this protocol will also be the authors of the final report. All authors have made substantive contributions to the design of the study. Additionally, all authors will have made substantive contributions to the interpretation of the data collected and the writing of the final report.

### Reproducible research

This protocol will be available to researchers via open-access publication. The dataset collected will be deidentified and made available on OSF. Similarly, the statistical syntax code used will be made available on OSF. These will be made available no later than 1 year on completion of data collection.
